## Methods

The BRIC study is a cross-sectional pre-post intervention study. Two different consecutive groups of bereaved relatives, cohort 1 and 2, will be approached to participate in a single-site study to compare complicated grief, anxiety, depression, posttraumatic stress and experiences with bereavement care. Cohort 1 will receive the standard of care, including ICU nurses’ presence and support for relatives, explanation of the process of dying and death, and empathic communication skills. Cohort 2 will receive additional bereavement support through a newly developed multicomponent nurse-led intervention.

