#### Study cohorts and time points

Both cohorts will be performed in study samples of 200 relatives per group, all participants will be invited to complete questionnaires measuring complicated grief, anxiety, depression and posttraumatic stress. Cohort 1 includes all reported first and second contact persons of patients who died in the ICU in 2018, which will serve as a pre-intervention baseline measurement. Eligible relatives were approached from March to May 2019 (−t_1_) and participants received the questionnaires directly after they signed the consent form (t_0_). The intervention was conducted from June 2019 onwards. Cohort 2, including all bereaved relatives in the ICU from October 2019 until March 2020, will serve as a post-intervention follow-up measurement. Eligible relatives will be approached 12 weeks after the death of their loved one (−t_2_) and participants will receive the questionnaires directly (t_1_) and at 6 months (t_2_) after they signed the consent form. The study design and timeline is presented in Fig. 1. For each deceased patient, up to 3 relatives can be included in the study. This recruitment process has been shown feasible in a previous study [39].

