#### Statistical analysis

Power and feasibility: Baseline (retrospective; t_1_) and follow-up measurements (6 weeks; t_2_ and 6 months; t_3_) will be performed in study samples of 200 relatives per group. These numbers are feasible, starting from a mean of 325 ICU deaths each year in the study setting, given a (2x) 12-month inclusion period, an expected 1.5 loved one per death, and an expected inclusion rate of 50% at 6 weeks and a retention rate of 80% at 6 months. These numbers ensure an effect size of 0.5 with a GPower t-test for the ´difference between two independent means´ (1-β = 95%, *p* < .05, two-tailed, d = .5) [48].

Analyses: Descriptive statistics (e.g., means, medians, or proportions as appropriate) and Student’s T-test between pre-post groups on demographic variables (e.g., gender, age, educational level) and outcome measures (e.g., complicated grief, anxiety, depression, posttraumatic stress, experiences with care) will be used to present noticeable differences between the baseline and intervention groups. Missing data will be handled using the multiple imputation. The scores will be analysed based on original data, and when available, according to established cut-offs. All test will be bilateral and significance will be defined as *p* < .05.

To test the hypotheses repeated measure analyses of variance (ANOVA) will be conducted with time as the within-subject factor (pre- versus post-intervention) and group (cohort 1 and 2) as the between-subject factor. Cohen’s d will be calculated to present effect sizes if applicable. Hierarchical regression analyses will be performed to explore determinants and identify subgroups (such as gender, ethnicity, risk profiles, relationship with patient) of bereaved relatives in the ICU who are at particular risk of developing mental health problems (i.e., those with scores above established cut-offs). Covariates, such as reason of admission, severity of illness, cause of death, bereavement care, time to say goodbye and social support, will be included in the regression model. This model will be adapted for cluster effects to correct for multiple relatives per deceased patient.

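### The test named for the hypotheses uses pre/post as a within-subject factor, but no relative is measured both before and after the intervention

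*Protocol article*

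**What the plan says.** The Methods section gives the design: "The BRIC study is a cross-sectional pre-post intervention study", and "Two different consecutive groups of bereaved relatives, cohort 1 and 2, will be approached to participate in a single-site study". Cohort 1 receives standard care; cohort 2 also receives the new intervention.

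The section on study cohorts and time points gives the schedule. Cohort 1 consists of relatives of "patients who died in the ICU in 2018, which will serve as a pre-intervention baseline measurement". They were approached from March to May 2019, and "participants received the questionnaires directly after they signed the consent form (t_0"). No later questionnaire is described for them. The intervention ran from June 2019. Cohort 2 covers deaths from October 2019 to March 2020, is called the post-intervention measurement, and is surveyed at t1 and t2.

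The Statistical analysis section then says: "To test the hypotheses repeated measure analyses of variance (ANOVA) will be conducted with time as the within-subject factor (pre- versus post-intervention"). Its between-subject factor is cohort. This is the sentence that introduces the test of the hypotheses.

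Other between-cohort comparisons are also mentioned:
- Statistical analysis lists Student's t-tests between the pre and post groups on the outcome measures.
- The Abstract says that baseline to follow-up differences will be adjusted by regression.
- The Efficacy row of Table 2 describes a covariate-corrected before/after comparison.
- The power statement uses a two-sample t-test on independent means.

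**The concern.** A within-subject pre/post factor needs people who were observed on both sides of the intervention. By design there are none here. The sentence that names the hypothesis test therefore describes a model that the data cannot support, and it disagrees with the test on which the study was powered.

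An analyst who holds to the text has no result to report and must choose a replacement. If that choice is made after the data are seen, the main comparison is no longer prespecified. The choices left open are the cohort 2 time point, the covariates and the treatment of clustering, and each can move the estimate.

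**Working it through.** **1. Measurements against the factor levels** (from Methods and from Study cohorts and time points)

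| | Pre-intervention value | Post-intervention value | Relatives with both |
|---|---|---|---|
| Cohort 1 (planned 200) | t0 | none | 0 |
| Cohort 2 (planned 200) | none | t1, t2 | 0 |

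**2. The model as written.** Let cohort = 0 or 1 and post = 0 or 1:

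mean = b0 + b1·cohort + b2·post + b3·cohort·post

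Every cohort 1 row is (1, 0, 0, 0) and every cohort 2 row is (1, 1, 1, 1). There are only two distinct rows, so the rank is 2 of 4. Only b0 and the sum b1 + b2 + b3 can be estimated. That sum is the plain difference between cohorts; the time effect and the interaction cannot be separated from it.

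**3. Time recoded as measurement wave.** The article does not state this model, but it is the obvious repair. The distinct rows become (1, 0, 0, 0), (1, 1, 0, 0) and (1, 1, 1, 1), so the rank is 3 of 4. Only b2 + b3 is identified for time. This is cohort 2's own change from t1 to t2. Both values come after the intervention, so that change reflects the natural course of grief and is not an intervention effect.

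**4. The plan's own power figure.** Inputs from Statistical analysis: d = 0.5, two-sided 0.05, power 95%, independent means.
- n per group = 2(1.960 + 1.645)² / 0.5² = 104 (105 with the exact t distribution).
- With 200 per group the power is 99.9%.
- So 200 is not the output of this calculation, but it exceeds the requirement. It is close to the feasibility product 325 × 1.5 × 0.50 × 0.80 = 195.

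What matters here is that the calculation is between-cohort throughout. It does not correspond to the ANOVA.

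**5. Power of a between-cohort test at d = 0.5**

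| Relatives analysed | Power | Detectable d at 95% power |
|---|---|---|
| 200 vs 200 | 99.9% | 0.36 |
| 200 vs 160 (80% retention in cohort 2) | 99.7% | 0.38 |
| 160 vs 160 | 99.4% | 0.40 |

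The article gives no correlation between relatives of the same patient. I assume 0.1 to 0.5 with 1.5 relatives per patient:
- Design effect = 1 + 0.5 × ICC = 1.05 to 1.25.
- At 200 per group, power is 99.8% to 99.4%.
- Retention and the largest design effect together give 200/1.25 = 160 against 160/1.25 = 128. By the normal approximation, 0.5/√(1/160 + 1/128) = 4.22, and 4.22 − 1.96 = 2.26, so power is about 98.8%.

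**6. Time since loss**
- Cohort 1: from a death at the end of December 2018 approached in early March 2019 (about 2 months) to a death in early January 2018 approached at the end of May 2019 (about 17 months).
- Cohort 2 at t2: 6 months post-loss according to the legends of Table 1 and Fig. 1. Under Study cohorts and time points it is 6 months after consent, following an approach at 12 weeks: 12 weeks (about 2.8 months) + 6 months, or about 9 months.

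On either reading t2 is nearly fixed while cohort 1 is spread widely. A covariate for time since loss therefore takes its slope almost entirely from cohort 1.

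**The case against.** The strongest reply is that the study's comparison is intact. Between-cohort t-tests on the outcomes are planned, with a two-sided 5% level set for all tests. Regression adjustment appears in the Abstract and in Table 2, the power basis is independent means, and the regression model is to be adapted for clustering. This stands, and it limits the point to a mis-specified sentence that conflicts with the rest of the plan. It does not remove the point. The t-tests are there to present differences and the hierarchical regression to explore determinants and subgroups; only the ANOVA is introduced as the test of the hypotheses.

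The power paragraph could also be read as giving both groups three measurements. The cohort section excludes this for cohort 1. Even repeat questionnaires in cohort 1 would not supply a value after exposure, because that cohort receives standard care only.

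A reader might infer more: that the ANOVA would drop cohort 1 and report cohort 2's time trend as the intervention effect, or that multiple imputation would invent a second measurement for all of cohort 1. The article supports neither. As written, the factor leaves no complete case in cohort 2 either, so the test fails visibly. Both outcomes need time to be recoded as t1 versus t2, which the article does not propose. Its imputation sentence refers only to missing data and does not suggest filling in measurements that were never scheduled.

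**Conclusion.** The point holds. The named hypothesis test cannot be estimated: pre/post is completely aliased with cohort, with 0 contributing relatives in either cohort and rank 2 of 4. It also contradicts the stated design and the power basis. This rests only on the schedule in the article's text; it does not depend on the missing figures, the sample size or any assumed correlation.

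It should not be read as saying that the cohorts cannot be compared. A between-cohort analysis is estimable, is already partly described, and has ample power for d = 0.5 at the planned numbers, given the ICC range assumed above. Confounding by calendar period and by time since loss remains whichever between-cohort model is chosen. Time since loss needs explicit handling because the cohorts overlap poorly on it.

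**What to change.** Replace the ANOVA sentence with one between-cohort regression named as the test of the hypotheses:
- Outcome score regressed on cohort (1 vs 2), adjusted for prespecified covariates, with the correction for relatives of the same patient that the section already plans for its regression. Report the cohort difference with a 95% confidence interval, and use the same form for each outcome.
- Compare cohort 1's t0 with one prespecified cohort 2 measurement, t2.
- Reconcile the timing of t2 between the legends of Table 1 and Fig. 1 and the cohort section. Align the time-point labels in the power paragraph (t1, t2, t3) with those used elsewhere (t0, t1, t2).
- Include time since loss as a covariate. Because that adjustment leans on a slope from cohort 1, add a sensitivity analysis restricted to cohort 1 relatives whose time since loss is similar to cohort 2's at t2.
- Report cohort 2's t1-to-t2 change as descriptive only.
- State that multiple imputation does not extend to measurements that were never scheduled.

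The cost is one rewritten paragraph and no new data. Intervals will be somewhat wider after clustering and adjustment, and the sensitivity analysis will use a smaller cohort 1. The Study status section reports that cohort 2 recruitment had been postponed and not yet begun, so the change could be made before any cohort 2 outcome was seen.

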### Study population

The study population consists of bereaved relatives after the death of an adult (age ≥ 18) ICU patient who fulfil all inclusion criteria and none of the exclusion criteria. Hospital records are used to identify the patients’ relatives, i.e., the first and second contact persons. Respondents will be selected using four criteria: 1) their loved one had died in the predefined period; 2) they were present during the ICU stay preceding death; 3) they have sufficient knowledge of the Dutch language (to read and understand information on the study and the questionnaires); and 4) they are considered legally responsible. Relatives with unknown contact details will be excluded.

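### The correction for several relatives of one deceased patient is planned only for the determinants regression, not for the cohort comparison that tests the hypotheses

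*Protocol article*

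**What the plan says.** All references are to the protocol article.

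- **Who enters.** Study population identifies relatives from hospital records as "i.e., the first and second contact persons", which is two per patient. Study cohorts and time points says "For each deceased patient, up to 3 relatives can be included in the study". Statistical analysis expects 1.5 per death.
- **Sample size.** Measurements "will be performed in study samples of 200 relatives per group", justified by a t-test for the "difference between two independent means" with d = 0.5 and 95% power.
- **Group comparisons.** Statistical analysis plans a Student's "T-test between pre-post groups on demographic variables", and the same sentence goes on to the outcome measures. The hypotheses are then assigned to a repeated-measures ANOVA with time within subjects and cohort between subjects. "All test will be bilateral and significance will be defined as *p* < .05".
- **Clustering.** A hierarchical regression follows, whose stated purpose is to explore determinants and find relatives at particular risk. Covariates go into that model, and the next sentence reads "This model will be adapted for cluster effects to correct for multiple relatives per deceased patient". Clustering is mentioned nowhere else.

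**The concern.** Relatives of one patient share the same death, the same staff and the same bereavement care, so their grief and distress scores are plausibly correlated. The article recognises this, because it plans a correction. It attaches that correction to the exploratory model and leaves it off the analyses that compare the cohorts.

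The omission matters for this contrast in particular. Cohort is a property of the deceased patient, so every relative of a patient sits on the same side of the comparison. Positive correlation then inflates the variance of the cohort difference, and a t-test or between-subject F-test that counts each relative as a separate unit does not see it. P-values come out too small and confidence intervals too narrow for the effectiveness claim.

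**Working it through.** **1. The plan's own figure.** Inputs from Statistical analysis: d = 0.5, 95% power, two-sided 5%, two independent means. The normal approximation gives 104 per group and the exact noncentral t gives 105. The planned 200 is therefore more than these inputs require. It gives 99.9% power, or 99.4% with the 160 left after the expected 80% retention (200 × 0.80).

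**2. Formulas.** For clusters of size m lying wholly within one cohort:

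- weighted cluster size m* = Σm² / Σm
- design effect DE = 1 + (m* − 1) × ICC
- effective number = n / DE
- actual error of an uncorrected nominal 5% test = 2 × [1 − Φ(1.96 / √DE)]

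**3. Cluster size.** The mean of 1.5 per death is from the article. Splitting it into half singles and half pairs is an assumption.

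- If 1.5 describes the relatives who take part: m* = (1 + 4) / (1 + 2) = 5/3.
- If 1.5 describes eligible relatives, each taking part independently with the expected 50% inclusion: a death with one eligible relative contributes E(m) = 0.5 and E(m²) = 0.5. A death with two contributes E(m) = 1 and E(m²) = 0.5 × 1 + 0.25 × 4 = 1.5. So m* = (0.5 + 1.5) / (0.5 + 1) = 4/3.

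**4. Results.** The ICC is not in the documents; 0.1 to 0.5 is an assumed range.

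| Pattern | m* | ICC | DE | 200/DE | 160/DE | Actual error |
|---|---|---|---|---|---|---|
| Independent response | 4/3 | 0.1 | 1.033 | 194 | 155 | 5.4% |
| | 4/3 | 0.3 | 1.100 | 182 | 145 | 6.2% |
| | 4/3 | 0.5 | 1.167 | 171 | 137 | 7.0% |
| Half singles, half pairs | 5/3 | 0.1 | 1.067 | 188 | 150 | 5.8% |
| | 5/3 | 0.3 | 1.200 | 167 | 133 | 7.4% |
| | 5/3 | 0.5 | 1.333 | 150 | 120 | 9.0% |

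**5. Bounds.** If every cluster were a pair, DE would be 1.10 to 1.50 and the error 6.2% to 11.0%. If every cluster reached three, DE would be 1.20 to 2.00 and the error 7.4% to 16.6%. Neither fits the plan's expected mean of 1.5. They show only why the permitted cluster size should be stated once.

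**6. Power after clustering.** At DE = 1.333 the need is 105 × 4/3 = 140 per group, still below both 200 and 160. Power is 99.1% with 200 and 97.2% with 160.

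**The case against.** **The regression may be the effectiveness analysis.** The abstract says that pre-post differences will be adjusted by regression, and the Efficacy row of Table 2 speaks of a covariate-corrected before-after comparison. The only covariate model described is the one that receives the cluster correction, so the authors may have meant the adjusted cohort effect to come from it. This shows that the text is loose, but it does not remove the point. Neither place mentions clustering, and Statistical analysis gives hypothesis testing to the ANOVA and does not name cohort as a term in the regression.

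**The t-tests are presentational.** They stand beside the descriptive statistics. That is fair, and the weight of the point rests on the ANOVA. The t-tests do cover the outcome measures, however, and the significance rule applies to all tests.

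**The error formula is for a comparison of means.** This stands. For a time or group-by-time term, the relevant correlation is between relatives' changes, and no value for that is assumed here. The percentages describe a between-cohort comparison only.

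**Two stronger readings do not hold.** A reader might infer from the power statement, which ignores clustering, that the study is too small. At 1.5 relatives per death it is not, as step 6 shows. Only the bound with three relatives in every cluster and an ICC of 0.5 takes 200 below 105 (200 / 2.00 = 100; 80 of the 160 retained), and the plan does not expect that. A reader might also infer that a third relative could enter cohort 2 only, because cohort 1 is described by first and second contact persons and cohort 2 as all bereaved relatives. Study population defines one population for both cohorts, and the limit of three is stated for the whole study. Differential entry is therefore a guess from loose wording.

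**Conclusion.** The point holds as an analysis defect of modest size. As written, the cluster correction reaches the determinants regression but not the comparison that carries the effectiveness claim. The direction is clear for any positive within-patient correlation: standard errors of the cohort difference are understated. The size rests on an ICC that the documents do not give. Over 0.1 to 0.5 the nominal 5% becomes roughly 5.4% to 9.0%, depending also on how relatives of one patient respond. A narrower range that starts at 6% would require ruling out low ICCs, for which the documents give no basis.

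The sample size needs no change on this account. Separately, two contact persons in Study population and up to three relatives in Study cohorts and time points contradict each other.

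**What to change.** - State in Statistical analysis that the patient-level correction applies to every between-cohort outcome comparison used to support effectiveness, by a random intercept for the deceased patient, GEE or cluster-robust standard errors. If the regression is meant to give the effectiveness estimate, say so and name cohort as a term in it.
- Give one maximum number of relatives per patient and one rule for which relatives qualify, and apply both to the two cohorts alike. Study status reports that recruitment of cohort 2 has been postponed and not yet started, so the wording can be settled before those data exist.
- Stating an assumed ICC and design effect beside the power figure would be good reporting, but it changes no decision.

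The cost is a change of wording and slightly wider confidence intervals. No extra data or participants are needed.

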#### Study status

The study is currently ongoing with recruiting relatives, which started with cohort 1 on March 1st 2019. Subsequently, the intervention has been developed as scheduled (Fig. 1) and implemented in daily practice accordingly. Recruiting of respondents for cohort 2 has been postponed because of the COVID-19 pandemic and will start immediately after management consent.

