#### Procedure

Consecutive ICU patients dying in the ICU between January 2018 and March 2020 will be identified from the ICU database. Descriptive data such as age, gender, length of stay, cause of illness and date of death will be extracted. Eligible relatives will be approached by telephone, where they are informed about the study and invited to participate in a survey exploring their current health situation and experiences with the quality of bereavement care. If interested, contact details such as email or postal address will be gathered to send additional written information and an informed consent form. After receiving the bereaved relative’s signed consent form, questionnaires will be send according to the participants’ preference of a digital version of the questionnaires or paper version with a stamp-free envelope.

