**Fig. 1 Fig1:**
[figure not shown]
BRIC study design. BRIC Bereavement in Relatives in the Intensive Care; t_0_ baseline measurement; t_1_ 6 to 8 weeks post-loss; t_2_ 6 months post-loss; TGI-SR Traumatic Grief Inventory-Self Report Version’; HADS Hospital Anxiety and Depression Scale; IES-R ‘Impact of Events Scale-Revised’; CQI R-ICU ‘Consumer Quality Index Relatives in the ICU’; QODD ‘The Quality of Dying and Death questionnaire’; RE-AIM model; Reach, Efficacy, Adoptation, Implementation and Maintenance

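### Cohort 2 recruitment is postponed but its death window and post-loss schedule are unchanged: the first questionnaire cannot be taken at its stated time for most or all relatives, and pandemic conditions at completion coincide with cohort

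*Protocol article*

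**What the plan says.** The Study status section of the protocol article reports: "Recruiting of respondents for cohort 2 has been postponed because of the COVID-19 pandemic and will start immediately after management consent". It gives no new start date, death window or measurement times.

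The design sections are unchanged:

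- **Window.** Study cohorts and time points states: "Cohort 2, including all bereaved relatives in the ICU from October 2019 until March 2020, will serve as a post-intervention follow-up measurement". The Abstract gives the same window, and Procedure also closes it in March 2020: "Consecutive ICU patients dying in the ICU between January 2018 and March 2020 will be identified from the ICU database".
- **Approach.** Study cohorts and time points states: "Eligible relatives will be approached 12 weeks after the death of their loved one". The first questionnaire (t1) follows directly. The second (t2) comes at 6 months, which that sentence counts from consent.
- **Labels.** The legends of Table 1 and Fig. 1 define the times differently: "t_1_ 6 to 8 weeks post-loss; t_2_ 6 months post-loss". Statistical analysis shifts the labels again: "follow-up measurements (6 weeks; t_2_ and 6 months; t_3_) will be performed in study samples of 200 relatives per group".

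Cohort 1 consists of relatives of patients who died in 2018. They were approached from March to May 2019 and measured once, directly after consent. The comparison is non-randomised, with cohort as the between-subject factor. The covariates named as examples in Statistical analysis include neither calendar period nor time since the death. The Limitations section does not mention the pandemic.

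**The concern.** A first measurement fixed at 6, 6 to 8 or 12 weeks after a death cannot be taken once that time has passed. The window closed in March 2020 and recruitment had not begun, so the schedule and the status report cannot both be carried out. This matters in two ways.

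**Meaning of the first questionnaire.** Grief, anxiety, depression and posttraumatic stress may change with time since loss, and the Discussion claims the longitudinal follow-up as a strength. Statistical analysis relies on a repeated-measures ANOVA. Cohort 1 has one measurement, so only cohort 2 can supply repeated ones, and its early one slips to an unstated time. The follow-up call that the plan gives as an example falls at 4 months. A 12-week questionnaire precedes such a call, whereas one at 4.6 months or later follows it.

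**Period effect.** Cohort 1 was approached wholly in 2019. Cohort 2 will be questioned wholly after a delay that the pandemic caused. Conditions at completion may affect the same outcomes that the intervention targets, and a difference in either direction could be credited to the intervention.

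**Working it through.** The article gives no figure for this point, so the check is calendar arithmetic on its stated dates.

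**Inputs.** Cohort 2 deaths from 1 October 2019 to 31 March 2020, which is 31+30+31+31+29+31 = 183 days (Study cohorts and time points). First measurement at 6, 6 to 8 or 12 weeks (Statistical analysis; legends of Table 1 and Fig. 1; Study cohorts and time points). Publication on 18 August 2020. Deaths are counted as evenly spread over the window (assumption).

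**Step 1: last possible dates.** The last death date, 31 March 2020, plus 42, 56 and 84 days gives 12 May, 26 May and 23 June 2020. Six months after it is about 30 September 2020.

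**Step 2: share of the window already past.** The status text is undated, so a range is shown. The share is (death dates more than 84, or 183, days back) / 183.

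| Date | Past 12 weeks | Past 6 months |
|---|---|---|
| 31 March 2020 | 98/183 = 54% | 0% |
| 30 April 2020 | 128/183 = 70% | 29/183 = 16% |
| 31 May 2020 | 159/183 = 87% | 60/183 = 33% |
| 24 June 2020 | 183/183 = 100% | 84/183 = 46% |
| 18 August 2020 | 183/183 = 100% | 139/183 = 76% |

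At publication the deaths lie 140 to 322 days back (20 to 46 weeks, or 4.6 to 10.6 months).

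**Step 3: time since loss in cohort 1.** The shortest gap from death to approach is 31 December 2018 to 1 March 2019, 60 days. The longest is 1 January 2018 to 31 May 2019, 515 days. The range of 140 to 322 days lies inside 60 to 515, so the cohorts overlap and adjustment for time since loss is possible.

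**Step 4: period.** All cohort 1 approaches fall in March to May 2019 and all cohort 2 questionnaires after the postponement. An indicator for pandemic conditions at completion would be identical to the cohort indicator, so a model cannot estimate both.

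**Step 5: illustration of what is at stake.** The article gives no size for a period effect, so the shifts below are assumptions. With the planned 200 per group, taken as independent, a two-sided t-test at 0.05 has 398 degrees of freedom, critical value 1.966 and noncentrality shift × √(200/2) = 10 × shift.

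| Assumed period shift (SD) | Rejection rate with no intervention effect | Power for true d = 0.5 if the shift opposes it |
|---|---|---|
| 0 | 5% | 99.9% |
| 0.1 | 17% | 98% |
| 0.2 | 51% | 85% |
| 0.3 | 85% | 51% |

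**The case against.** The strongest reply has four parts.

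1. **Questionnaires can still be collected.** Study cohorts and time points times them from consent. That stands. A reader might infer that the first measurement is lost altogether, but the article does not support this. What fails is its stated time after the death. The second measurement is also only partly affected: at publication, deaths from about mid-February 2020 could still reach 6 months post-loss, and 6 months counted from consent remains obtainable for all. The conflict between a 12-week approach and a 6-to-8-week label existed before the delay.

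2. **Time since loss is not tied to cohort.** A reader might infer that the delay makes the two inseparable. Step 3 shows the opposite: cohort 1 spans about 60 to 515 days and contains the delayed cohort 2 range. The mismatch was there from the start, and the delay brings the cohorts closer together.

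3. **The start date is unknown.** Management consent could have come between writing and publication, so 100% and 76% are not established facts. This stands, and is why a range is shown. Even the earliest date in the table leaves more than half the window past 12 weeks.

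4. **The window has not been moved.** A reader might argue that a later window would put every death under pandemic conditions and alter who meets the criterion "they were present during the ICU stay preceding death". No section moves the window, and visiting restrictions appear nowhere, so this would criticise a plan that the article does not contain.

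The article is also a condensed account, and Ethical considerations says that modifications go to the ethics committee by amendment. A revised schedule may therefore exist elsewhere. The article nevertheless states two things that cannot both be carried out.

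**Conclusion.** The point holds in this form. For the stated window, the post-loss time of the first cohort 2 questionnaire cannot be met for most or all relatives: 54% to 100% of death dates are past 12 weeks, depending on when between 31 March and 18 August 2020 recruitment starts. This assumes that the window is meant as written and deaths are evenly spread.

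Separately, pandemic conditions at completion coincide fully with cohort, so no covariate can remove their effect. This follows from the design and does not depend on the exact start date. Its size and direction are not in the documents, and the rejection rates in the working illustrate assumed shifts only. The article neither deals with this effect nor lists it as a limitation.

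**What to change.** 1. **Reconcile the schedule.** Bring the Abstract, Table 1, Procedure, Study cohorts and time points, Fig. 1, Statistical analysis and Study status into agreement: one cohort 2 death window, one set of achievable measurement times and one set of labels, each stated as counted from death or from consent.
2. **Record time since loss.** Collect actual days from death to completion in both cohorts and include them as a covariate in the cohort comparison.
3. **Prespecify a sensitivity analysis** that excludes cohort 2 deaths after pandemic measures began locally, with the date supplied by the hospital. This addresses conditions around the death. It does not remove conditions at completion.
4. **State the limitation** that pandemic conditions at completion cannot be separated from the intervention effect, and temper the effectiveness conclusion.
5. **If the early measurement is given up**, replace the repeated-measures ANOVA with a between-cohort regression, keeping the planned correction for several relatives per patient.

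**Cost.** An amendment, slightly wider intervals and a smaller sensitivity sample. On the article's own rates, a six-month window yields about 325/2 × 1.5 × 0.5 = 122 relatives before exclusions, not 200.

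Dropping t1 or restricting cohort 1 to a matched time range is optional and costs precision. With deaths and approaches evenly spread, about 50% of cohort 1 falls within 140 to 322 days, roughly 100 of 200. The stated d = 0.5 at 95% power needs 105 per group.
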